## Background

The success of any therapy is often based on the questions "Is it safe? Is it effective?". For chiropractic therapy there has been some research to ascertain effectiveness [1] and also for spinal manipulation [2] but there has been very little to document its safety. The safety profile of any therapy is a cornerstone of modern practice as it provides protection for the public and informs the consumer consent process. Trials of chiropractic therapy have shown mixed results which, together with its current use for multiple indications, make research into aspects of its safety important.

There are several published reports about the safety of chiropractic treatment. A single arm study conducted by Senstad et al in 1996 [3] reviewed the type, frequency, and characteristics of unpleasant side effects after spinal manipulation. About half of the patients reported at least one adverse event some time during the course of a maximum of six treatments. Of these, the most common adverse events were local discomfort (53%), headache (12%), tiredness (11%), or radiating discomfort (10%). Adverse events were mild or moderate in 85% of patients. Limitations of this study included that the chiropractors gathered their own data; responders could not be compared with non-responders; and reports could not be obtained from patients who attended one treatment only. It is possible that some opted out because of unpleasant reactions, potentially making the results an underestimate.

Hurwitz et al compared the rate of adverse events between two randomly allocated groups of neck patients who received either manipulation or mobilisation from chiropractors [4]. About a third of all participants reported at least one adverse event. The most common adverse events were increased pain (27%), headache (15%), tiredness (12%), radiating pain (6%), and dizziness (4%). Participants who received manipulation were more likely to experience an adverse event than participants who received mobilisation.

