### Withdrawing Participants from this Study

A stopping rule was defined for withdrawing participants from this study in accordance with recommendations in the CONSORT extension for Better Reporting of Harms [11]. If a participant reports to their chiropractor or research staff a severe adverse event they will be withdrawn from the study and referred to their local doctor or hospital emergency department depending on the nature of the event. Each participant will complete an adverse event questionnaire two days after each chiropractic appointment and asked to then return it in a reply paid envelope. Any adverse event will be classified as severe if it is thought to be an emergency situation e.g. stroke or the associated pain intensity is rated above 8/10 on an 11 point NRS, which accords with the definition for a serious adverse event by Rubinstein et al [6].

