#### Analysis of Adverse Events

The primary outcome (adverse event; yes/no) will be compared between groups. The severity and frequency of adverse events will be reported descriptively. Logistic regression will be used to examine associations between adverse events and several factors. Factors which have been significantly associated with adverse events in previous studies will be selected for this study. These factors comprise treatment satisfaction [4], manipulation/mobilisation [4], global improvement [4], GP visit in last six months [6], duration of neck/back pain [6], medication use [29], gender [29], and age [29]. The relative risk [39] will be calculated using a two by two contingency table and 95% confidence intervals. The number needed to harm [40] will be calculated with 95% confidence intervals to identify the number of individuals needed to be exposed to a risk factor (chiropractic treatment) over a specific period to cause harm (adverse outcome) in one patient that would not otherwise have been harmed. Data will be assessed by using per protocol analysis. In addition, an intention to treat analysis will be undertaken by using sequential regression multiple imputation [41].

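### The first-named analysis of the primary safety outcome is per protocol, although a severe adverse event leads to withdrawal, so the outcome itself can cause exclusion

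*Protocol article*

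**What the plan says.** Under Analysis of Adverse Events the protocol article fixes the outcome: "The primary outcome (adverse event; yes/no) will be compared between groups". The same paragraph then names the analysis sets: "Data will be assessed by using per protocol analysis. In addition, an intention to treat analysis will be undertaken", the second of these with multiple imputation. It does not call either one primary and does not say who belongs to the per-protocol set.

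Under Withdrawing Participants from this Study: "If a participant reports to their chiropractor or research staff a severe adverse event they will be withdrawn from the study". An event is severe if it is an emergency or if "the associated pain intensity is rated above 8/10 on an 11 point NRS". The same section has participants complete a questionnaire two days after each appointment.

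The course of treatment is two sessions at least one week apart (Abstract, Methods). Those who discontinue are followed up to learn why they stopped (Treatment allocation). The first aim is to establish how often adverse events occur, and how severe they are, relative to sham (Aims). In the Background, the article says of an earlier single-arm study: "It is possible that some opted out because of unpleasant reactions, potentially making the results an underestimate".

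**The concern.** A per-protocol set normally contains those who completed the planned course, here two treatments. A participant withdrawn for a severe event after the first visit has not completed it, and neither has one who stays away after an unpleasant first session. Both would leave the first-named analysis of adverse events because they had an adverse event. Membership of the analysis set then depends on the outcome, and the comparison is no longer between the groups as randomised.

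The active-arm event rate and the risk difference would be understated, and the number needed to harm (NNH) overstated. The severity description could lose some of its most severe cases. The Background shows that the authors know that people who leave because of a reaction can make harm look rarer.

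The planned intention-to-treat analysis repairs this only if the reported events of withdrawn participants stay in it as observed values. The article does not say whether they do.

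**Working it through.** **Inputs from the protocol article.** Event rates 45% (usual care) and 25% (sham), two-sided alpha 0.05, 90 per group, 80% power (Sample Size). Severe share 13% of adverse events in one cited prospective study of neck-pain patients (Background).

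**Assumptions.** The 13% is a share of events; it is used here as the share s of participants with an event who are severe and withdrawn. The sham-arm share is not given, so it is varied from zero to equal. The split by visit is not given either; half of the severe events are taken to follow visit 1, so s = 6.5% for that case.

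**Step 1: reproduce the plan.** With pooled variance and no continuity correction,

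n = [1.960·√(2·0.35·0.65) + 0.842·√(0.45·0.55 + 0.25·0.75)]² / 0.20² = 88.1, that is 89 per group.

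Power at 90 per group is 80.8%. The stated sample size is sound and is not in question. With everyone counted, the risk difference (RD) is 20.0 points, the relative risk (RR) 0.45/0.25 = 1.80, and NNH 1/0.20 = 5.0.

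**Step 2: leave out the withdrawn severe cases.** For an arm with event rate p, the share removed is ps. The remaining rate is p(1 − s)/(1 − ps) and the remaining number is 90(1 − ps).

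Example, active arm, s = 13%: ps = 0.45 × 0.13 = 0.0585, about 5.3 of some 40 participants with an event. The rate becomes (0.45 − 0.0585)/(1 − 0.0585) = 0.3915/0.9415 = 41.6%.

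Example, sham arm, s = 13%: ps = 0.25 × 0.13 = 0.0325. The rate becomes 0.2175/0.9675 = 22.5%.

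**Step 3: effect measures and power** (same power formula, remaining numbers).

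| Severe cases left out | Active | Sham | RD (points) | RR | NNH | Power |
|---|---|---|---|---|---|---|
| None | 45.0% | 25.0% | 20.0 | 1.80 | 5.0 | 80.8% |
| Visit 1 only, equal shares (6.5%, 6.5%) | 43.3% | 23.8% | 19.6 | 1.82 | 5.1 | 79.1% |
| Visit 1 only, active arm only (6.5%, 0%) | 43.3% | 25.0% | 18.3 | 1.73 | 5.5 | 73.5% |
| All, equal shares (13%, 13%) | 41.6% | 22.5% | 19.1 | 1.85 | 5.2 | 77.0% |
| All, half the share in sham (13%, 6.5%) | 41.6% | 23.8% | 17.8 | 1.75 | 5.6 | 71.0% |
| All, active arm only (13%, 0%) | 41.6% | 25.0% | 16.6 | 1.66 | 6.0 | 64.6% |

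In every row with exclusions, the active-arm rate and the RD fall and NNH rises. RR falls in the rows where the severe share is larger in the active arm. Where the shares are equal it rises slightly.

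People who stop of their own accord after a non-severe event would add to the loss. The article gives no rate for them, so they are not quantified.

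**The case against.** The strongest reply is that the exclusion is inferred. The per-protocol set is undefined, and nothing in the article says that withdrawal discards data. A severe event triggers withdrawal because it has been reported, so the yes/no outcome is already known. An intention-to-treat analysis is planned as well. A reader might infer that the plan by construction strips severe events from the trial; the text does not support that. What remains is that the article does choose per protocol as the first-named analysis, and under its usual meaning these participants are left out. That is a stated choice, not a detail left for a later document.

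The reach is also limited. After a severe event at the second visit both treatments have been given, so exclusion is clear only after the first. On the 13% figure about 87% of events are not severe and trigger no withdrawal. Both points stand, and they confine the loss to some of the most severe harms plus an unknown number of voluntary stoppers.

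The loss need not be confined to the active arm. Severe includes pain above 8/10 in people enrolled with spinal pain, and the Background accepts that natural history can produce reported events. This stands, and it is why the size is a range.

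Finally, a reader might say that the trial repeats the fault it finds in the earlier study. That study could not obtain reports from people who attended only once; here a questionnaire follows each appointment, including the first. The collection gap is addressed. The choice of analysis set is not.

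**Conclusion.** The point holds in a limited form. The first-named analysis of the primary safety outcome can exclude participants because of that outcome, chiefly those withdrawn or stopping after the first visit, and this works against the aim of measuring how frequent and how severe harms are.

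If the 13% severe share applies to participants with an event, the RD falls from 20 points to between 19.6 (first-visit severe events only, equal shares in both arms; NNH 5.1, power 79%) and 16.6 (all severe events, active arm only; NNH 6.0, power 65%). The lower end needs no severe withdrawals at all in the sham arm and the exclusion of second-visit cases too. The upper end is close to negligible for the comparison, although severe cases would still be missing from it.

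A reader might infer that all effect measures are biased towards safety. That is so for the active-arm rate, the RD and NNH in every scenario examined, but not for RR. It ranges from 1.66 to 1.85 around the planned 1.80 and moves towards safety only when the loss is greater in the active arm.

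**What to change.** In Analysis of Adverse Events:

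- Name the comparison of all randomised participants, as allocated, as the primary analysis.
- Count as an observed yes any participant with an adverse event reported after either appointment or at withdrawal.
- Use the planned multiple imputation for participants who have no reported event and lack a questionnaire for a treatment they received. This includes a negative first report with a missing second, which should not be scored as no.
- Define the per-protocol set and keep that analysis as a sensitivity analysis.
- State that withdrawal for an adverse event does not remove reported events from the safety comparison.

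The cost is small: two analyses already planned change places, with slightly more imputation work. No extra questionnaires for withdrawn participants are needed. The clinical withdrawal rule is not addressed here.

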#### Analysis of Secondary Outcomes

The efficacy of short term usual chiropractic care will assessed in two ways. First, for the repeated measures ANOVA will be used to compare differences between groups for the pain and physical function measures. Second, the minimum acceptable outcome [14], which involves establishing what participants consider to be a "minimum acceptable outcome" for which they would undertake a procedure. The proportion of participants meeting this target in each group will be reported descriptively and the groups will be compared by using a chi-squared test [14].

Blinding to treatment allocation will be assessed by using the Bang Index (BI) [36] which will allow us to determine if a significant proportion of participants guessed that they were in opposite treatment group. A BI value of < -0.2 indicates that significant proportion guessed wrongly, BI between 0.2 and -0.2 indicates participants guessed randomly, and BI > 0.2 indicates that the study was unblinded.

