**Methods:**

One hundred and eighty participants will be randomly allocated to either usual chiropractic care or a sham intervention group. To be considered for inclusion the participants must have experienced non-specific spinal pain for at least one week. The study will be conducted at the clinics of registered chiropractors in Western Australia. Participants in each group will receive two treatments at intervals no less than one week. For the usual chiropractic care group, the selection of therapeutic techniques will be left to the chiropractors' discretion. For the sham intervention group, de-tuned ultrasound and de-tuned activator treatment will be applied by the chiropractors to the regions where spinal pain is experienced. Adverse events will be assessed two days after each appointment using a questionnaire developed for this study. The efficacy of short term chiropractic care for spinal pain will be examined at two week follow-up by assessing pain, physical function, minimum acceptable outcome, and satisfaction with care, with the use of the following outcome measures: Numerical Rating Scale, Functional Rating Index, Neck Disability Index, Minimum Acceptable Outcome Questionnaire, Oswestry Disability Index, and a global measure of treatment satisfaction. The statistician, outcome assessor, and participants will be blinded to treatment allocation.

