### Study Sample and Participant Enrolment

Participants will be recruited in Perth, Western Australia by the use of newspaper advertisements. Any person who responds to the advertisement by phone will be considered a potential candidate and will receive through the mail the following documents:

• an information letter;

• a pain diagram to assess symptom location and distribution;

• the Numerical Rating Scale (NRS) [12] on which the patients will score their current overall level of spinal pain;

• Functional Rating Index (FRI) [13];

• a questionnaire enquiring about the minimum amount of change in pain levels that potential participants would consider to be an acceptable outcome [14];

• a medical history checklist.

These documents will be returned in a reply paid envelope and the information will be used to determine eligibility. To be considered for inclusion, potential participants must be adults (18 years or older), literate in English, and have had spinal pain (neck pain, mid-back pain, or low back pain) for more than 1 week. In addition, potential participants must score at least 3 on the NRS and 12 on the FRI as this allows measurement of a minimal clinically important difference in the improvement direction [15].

Potential participants will be excluded if they:

• have been previously unable to tolerate common chiropractic treatments, for example: manipulation; mobilisation; Activator^®^; flexion distraction therapy; traction; soft tissue massage; trigger point therapy; sacro-occipital technique; ultrasound; interferential therapy; and Transcutaneous Electrical Nerve Stimulation (TENS).

• have any of the following conditions: spinal pain related to cancer or infection; clinically important fracture of the spine; spondyloarthropathy; known osteoporosis; progressive upper or lower limb weakness; symptoms of cauda equina syndrome or other important neurological condition; recent disc herniation; cardiovascular disease likely to be a contraindication to spinal manipulation; uncontrolled hypertension; cognitive impairment; blood coagulation disorder; spinal surgery in the last year; previous history of stroke or transient ischaemic attacks; have a pacemaker or other electrical device implanted; are currently pregnant;

• have a current compensation claim;

• have a substance abuse problem;

• cannot commit to study protocol.

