### Treatment allocation

When participants visit Murdoch University and after baseline measures and consent have been obtained, one of the research staff, excluding the research assistant (RA) and statistician, will randomly allocate the participants to one of the two groups using a 1:1 allocation. A statistician will generate a permuted block randomization sequence allocating persons to either chiropractic care or the sham group. The group assignment will be written on small cards and placed in opaque envelopes.

For ethical reasons, participants in the sham group will be offered two treatments of usual chiropractic care two weeks after receiving the last sham treatment and following receipt of their final outcome measures by the RA. Any participant who discontinues treatment will be followed-up to determine the reason for discontinuation.

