#### 2. Baseline Assessment

The following questionnaires will be administered at baseline: demographic questionnaire; NRS [12]; FRI [13]; Fear-Avoidance Behaviour Questionnaire (FABQ) [19]; SF-36 [20]; STarT Back Musculoskeletal Screening Tool [21]; and the Pain Catstrophising Scale (PCS) [22]. Also, the primary area of concern for each participant will be identified and one of the following questionnaires specific to that area will be administered: the modified Oswestry Disability Index (ODI) [23]; or Neck Disability Index (NDI)[24].

Descriptive statistics from the baseline measures including the SF-36, STarT Back Musculoskeletal Screening Tool, and demographic questionnaire will be examined to determine if clinically important differences are evident between the usual chiropractic group and sham group at baseline. The SF-36 is a well validated and extensively used measure of general health status [25]. The STarT Back Musculoskeletal Screening Tool is brief validated instrument that has been developed to identify people with chronic pain who are more likely to experience persistent symptoms [21]. The demographic questionnaire enquires about age, sex, race/ethnicity, education, household income, marital status, employment status, smoking, and alcohol and legal drug consumption. These items were derived from classifications used by the Australian Bureau of Statistics [26].

A baseline symptom checklist will be administered to examine whether the adverse events that participants reported after each chiropractic treatment were actually an adverse event or the persistence of a presenting complaint. This will be achieved through comparing data from the symptom checklist taken at baseline to data from the adverse event checklist collected after each chiropractic treatment.

The NRS contains an 11-point scale varying from 0 (no pain) to 10 (worst pain imaginable) [12]. It is a valid, reliable and responsive measure of pain intensity [27]. Participants will be asked to use the scale to rate: their worst level of pain in the last two days; average pain level in the last two days; best pain level in the last two days; and current pain.

The FRI contains 10 questions which enquire about the impact of neck and back pain on physical function. It was designed to assess conditions where more than one area of the spine is involved and is valid, reliable and responsive [13].

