#### 4. Assessment at Two Week Follow-Up

We will administer at two week follow-up the NRS [12], FRI [13], and the area specific instruments modified ODI [23] or NDI [24]. These questionnaires will be used to establish the short term efficacy of brief chiropractic care for spinal pain. The FABQ [19] and PCS [22] will also be administered to examine whether cognitive aspects related to the experience of pain influence pain severity, physical function and adverse events.

Also, a global measure of treatment satisfaction [27] and global measure of perceived change [35] will be administered at two week follow-up. The global measure of treatment satisfaction [27] will be used to examine the association between adverse events and treatment satisfaction. It will be measured on a five point categorical scale (very dissatisfied = 0; dissatisfied = 1; no preference = 2; satisfied = 3; very satisfied = 4). The global measure of perceived change [35] will be used to examine the association between adverse events and overall perceived change in the main complaint. It will be measured on an 11 point continuous scale varying from -5 to +5 (-5 = much worse, 0 = unchanged, +5 much better).

Blinding will be assessed at two weeks with a questionnaire [36] that asks the participants if they were in the real treatment group or the sham treatment group. The possible responses are: real treatment group; sham group; or don't know.

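### Pain and function: the planned repeated measures ANOVA on one baseline and one two-week value is valid, but adjusting the two-week score for baseline (ANCOVA) is generally more precise at no cost

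*Protocol article*

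**What the plan says.** The protocol's Analysis of Secondary Outcomes section states that "repeated measures ANOVA will be used to compare differences between groups for the pain and physical function measures". It names neither a baseline covariate nor the ANOVA term that will serve as the treatment test.

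The measurement schedule comes from three other sections.

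- Baseline Assessment: NRS and FRI are given to everyone. For the region-specific scale, "the primary area of concern for each participant will be identified and one of the following questionnaires specific to that area will be administered", namely the modified ODI or the NDI.
- Treatment allocation: randomisation takes place "after baseline measures and consent have been obtained", so the baseline values precede allocation.
- Assessment at Two Week Follow-Up: "We will administer at two week follow-up the NRS [12], FRI [13], and the area specific instruments" (ODI or NDI). No other post-treatment assessment of these scales is listed, and the abstract agrees: "The efficacy of short term chiropractic care for spinal pain will be examined at two week follow-up".

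Each scale therefore contributes one pre-randomisation value and one post-treatment value per participant.

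**The concern.** With only two time points, repeated measures ANOVA gains nothing from its repeated structure. Its group-by-time term compares mean change between the arms, which forces the coefficient on baseline to be 1. ANCOVA estimates that coefficient from the data, so in general it gives a narrower confidence interval from the same questionnaires. It also corrects the estimate for whatever baseline difference chance has produced.

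At stake is the precision of the second stated aim, efficacy against sham. The Sample Size section sets 180 participants for the adverse-event outcome alone and states no power for pain or function, so precision there should not be given away. A smaller point is that the sentence leaves open which ANOVA term is tested, and one of the two candidates would dilute the effect.

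**Working it through.** **The plan's own figure.** The only sample size is for adverse events: 45% against 25%, two-sided 0.05, 80% power, 90 per group. With pooled variance and no continuity correction, n = (1.96·√(2·0.35·0.65) + 0.8416·√(0.45·0.55 + 0.25·0.75))² / 0.20² = 88.1, so 89 per group; power at 90 is 80.8%. The figure reproduces and is not touched by this point. There is no corresponding figure for pain or function.

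**Step 1: what the ANOVA tests.** With two times, the group-by-time F equals the square of the t statistic on change scores. In a simulated data set with 90 per arm, both came to 8.357.

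**Step 2: variances.** Let s_pre and s_post be the SDs, k = s_pre/s_post, and r the baseline to follow-up correlation. Per participant, in units of s_post²:

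- change score: 1 + k² − 2rk
- ANCOVA (large samples): 1 − r²
- difference: (k − r)², which is never negative and is zero only when r = k

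The ratio of ANCOVA to change-score variance is (1 − r²)/(1 + k² − 2rk). At k = 1 it reduces to (1 + r)/2.

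**Step 3: numbers.** Both r and k are assumptions. The last two columns give the number of participants that change scores would need to match ANCOVA with 180, that is, 180 divided by the ratio.

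| r | ratio, k = 1 | ratio, k = 0.8 | N, k = 1 | N, k = 0.8 |
|---|---|---|---|---|
| 0.3 | 0.91/1.40 = 0.65 | 0.91/1.16 = 0.78 | 277 | 230 |
| 0.5 | 0.75/1.00 = 0.75 | 0.75/0.84 = 0.89 | 240 | 202 |
| 0.7 | 0.51/0.60 = 0.85 | 0.51/0.52 = 0.98 | 212 | 184 |

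The N columns apply to NRS and FRI, which everyone completes. ODI and NDI are each completed by only part of the sample; the ratios hold there too, but not the totals.

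**Step 4: power for an illustrative effect.** Assume a difference of 0.4 SD, 90 per arm and k = 1. Power for group-by-time against ANCOVA is 62% against 80% (r = 0.3), 77% against 87% (r = 0.5) and 93% against 96% (r = 0.7). Simulation with 4,000 runs gave 76.6% against 86.5% at r = 0.5, and 93.5% against 96.4% at r = 0.7.

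**Step 5: chance imbalance.** If the arms differ at baseline by b, the expected two-week difference given baseline is the treatment effect plus (r/k)·b. The change-score estimate is then off by (r/k − 1)·b. At r = 0.5 and k = 1, half of the imbalance enters the estimate with reversed sign. Over repeated randomisations this averages to zero.

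**Step 6: the group main effect, if that were the test.** It averages the pre- and post-treatment values, so an effect d becomes d/2. At k = 1 the variance of the average is (1 + r)/2, and efficiency relative to ANCOVA is (1 − r)/2: 0.35, 0.25 and 0.15 at r = 0.3, 0.5 and 0.7. Power at 0.4 SD would be about 38%, 34% and 31%.

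**The case against.** The strongest reply is that nothing here is an error. Under randomisation the group-by-time test is a valid, unbiased test of the treatment effect; it answers the second aim and does use the baseline, with slope 1. The aim is secondary, the minimum acceptable outcome gives a second route to it, and the gain depends on two unknown quantities. It almost disappears when r is close to k. All of this stands, and it limits the point to an improvement in precision.

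A reader might infer more, and the protocol does not support it:

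- *That the efficacy effect will be halved.* This needs the group main effect to be the chosen test. The protocol names no term, group-by-time is the usual choice in a two-arm pre/post design, and an article may leave that detail to a fuller document. The figures in step 6 are conditional on that reading.
- *That the entry thresholds bias the change scores.* The enrolment section says "potential participants must score at least 3 on the NRS and 12 on the FRI", and regression to the mean does follow from such thresholds. It is expected equally in both arms, though, and cancels in the group contrast. The thresholds also apply to mailed screening forms, ahead of the separate baseline assessment.
- *That ANOVA loses participants whom ANCOVA would keep.* Complete-case ANCOVA also drops anyone without a two-week value.
- *That a chiropractor term should be added alongside baseline.* The Discussion says that a different group of chiropractors delivers each intervention. Chiropractor is thus nested in arm, and as an ordinary fixed effect it would be collinear with group.

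**Conclusion.** The point holds as a free improvement to the secondary efficacy analysis. The planned group-by-time test is valid but generally less precise than ANCOVA on data already scheduled for collection, and it does not condition on chance baseline imbalance. Over the assumed range (r from 0.3 to 0.7, k of 0.8 or 1), the variance saved runs from about 2% to 35%. The direction is certain in large samples because the variance difference is a square; the size is not, because the protocol gives neither r nor the SDs. The untested-term ambiguity adds a modest reason to change the sentence, since naming ANCOVA rules out the diluted main effect.

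**What to change.** Replace the repeated measures ANOVA sentence with a linear model for each pain and function scale: the two-week score regressed on treatment group and the baseline-visit value of the same scale, reporting the adjusted mean difference with its 95% CI. Do not add chiropractor as a fixed effect. The sequential regression multiple imputation that the protocol describes under Analysis of Adverse Events may be extended to these outcomes, as a separate choice.

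The cost is one sentence in the analysis section. No new data, visits or participants are needed.
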